### Inclusion criteria

Patients with epithelial tumours of nasopharynx; nasal cavity and paranasal sinuses; salivary gland cancer in large and small salivary glands; and middle ear (i.e. squamous carcinoma; adenocarcinoma; neuroendocrine; adenosquamous carcinoma, teratocarcinosarcoma, NUT carcinoma, odontogenic tumours) + neuroendocrine and adenocarcinoma in hypopharynx; oropharynx; larynx; oral cavity and lip + odontogenic carcinoma in oral cavity.Adult patients (aged ≥18 years).Diagnosis performed or verified by the expert centre entering the patient information in the registry.Patients entering the HCP at any clinical phase of the disease (diagnosis, treatment of primary cancer, treatment of recurrence, treatment of M+ etc.). The HCP will collect information on the entire course of the disease regardless of when it started to manage the patient. The HCP can decide, based on its resources, the number of patients on whom it can collect data.New patients managed by the HCP from 2021 onwards plus patients managed by the HCP, who are actively followed up at the hospital, with year of diagnosis dating back to maximum 2018.

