### Outcomes

Primary outcomes with a time frame of 1 year include:

Overall survival (all cause and/or cause specific)Disease free survivalTreatment response: the percentage of patients whose cancer shrinks or disappears after treatment. Treatment response expressed as a complete response; partial response; stable disease; progression based on clinical judgment on imaging.Cancer treatment observed adverse events: incidence of cancer treatment adverse events as assessed by Common Terminology Criteria for Adverse Events (CTCAE)Surgical complications: percentage of patients with surgical complications as assessed by the Clavien-Dindo ClassificationQuality of care: percentage of patients treated according to clinical practice guidelines for head and neck cancer.

Predictors of mortality and/or tumor response include but are not limited to:

Patients’ Characteristics (age, gender, educational level, tobacco, comorbidity, virus status when appropriate)Tumor Characteristics (site, histology, T,N,M, clinical and pathological stage, tumour mutation)Treatment Characteristics (radiotherapy alone, surgery alone, systemic therapy alone, multimodal therapy)

Exposures will mainly include different type of treatment (radiotherapy alone, surgery alone, systemic therapy alone, multimodal therapy)

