### Ethical considerations

The registry was approved by the ethic committee of the Fondazione IRCCS Istituto Nazionale dei Tumori (INT) with protocol number (INT 43/21).

INT is the coordinator of the EURACAN registry as well as a data provider. At the INT, and at each HCP involved, responsible investigators ensure that the EURACAN registry will be implemented in compliance with the protocol, following the instructions and procedures described herein. Each HCP is a controller and will identify a data processor.

Patient protection

Personal data will be recorded and stored in pseudonymised format in a DB installed at the HCP level. Either the PHT solution will enable data sharing among multiple organizations without identifiable data leaving the HCP, or anonymised data will be sent to the INT.

All parties involved in registry development will maintain strict confidentiality to ensure that neither personal privacy nor the privacy of the families of patients participating in the registries will be violated. Data will be processed exclusively by authorized personnel participating in the EURACAN registry (a data processor will be identified at each HCP involved). Access to computer systems and the premises where they are kept will be controlled by appropriate security measures which comply with privacy regulation requirements. The processing of patients’ personal data taking part in the EURACAN registry, and specifically in relation to consent-related data, will comply with local privacy legislation and the General Data Protection Regulation 2016/679 (GDPR) of the European Union.

The registry protocol is submitted to the ethics committees (EC) of the HCPs involved. Furthermore, the ECs of the HCP involved will authorize in advance any research carried out using EURACAN registry data.

Informed consent

Written informed consent is the legal basis of the EURACAN registry and so is required from all participants.

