### Status and timeline of the registry

The registry initiated recruiting in May 2022. The estimated completion date is December 2030 upon agreement on the achievement of all the registry objectives. As of August 2022, the registry is recruiting.

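### The registry mixes incident patients with survivors diagnosed back to 2018, but fixes no time origin and does not recognise survivor selection, so survival counted from diagnosis would be too high

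*Protocol article*

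**What the plan says.** Under Inclusion criteria, the protocol article defines two groups: "New patients managed by the HCP from 2021 onwards" and "patients managed by the HCP, who are actively followed up at the hospital, with year of diagnosis dating back to maximum 2018". Entry is open to "Patients entering the HCP at any clinical phase of the disease", including recurrence and metastatic disease. For every patient, "The HCP will collect information on the entire course of the disease regardless of when it started to manage the patient".

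Under Status and timeline of the registry: "The registry initiated recruiting in May 2022". Completion is estimated for December 2030. Under Ethical considerations: "Written informed consent is the legal basis of the EURACAN registry and so is required from all participants".

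The Outcomes section opens its list with "Primary outcomes with a time frame of 1 year include". Overall survival and disease-free survival come first, and no time origin is given. The Data analyses plan names Cox models and propensity-score adjustment. The limitations in the Discussion name expert-centre representativeness, confounding and follow-up, and plan a comparison with population-based data that includes prognosis. Delayed entry, left truncation, a landmark, or a split between incident and prevalent cases is not mentioned anywhere.

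**The concern.** A patient diagnosed in 2018 to 2020 must be in active follow-up, and so alive, to be included. On the stated consent rule and start date, a patient first seen between January 2021 and April 2022 who died before May 2022 also appears to be lost. Those who do enter bring their history back to diagnosis. That interval is immortal time: the patient counts as at risk, but a death in it would have prevented inclusion.

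Overall survival is the first-listed primary outcome, so the effect falls on the registry's main result. Hazard ratios for factors that act early can also be distorted. The comparison of prognosis with population-based data would mix a true centre effect with survivor selection.

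Entry at recurrence or metastatic phase works the other way. For those patients the disease-free survival event came before entry and is the reason for it, and they are also selected for poor overall survival.

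**Working it through.** The document gives no survival rate, so there is no figure of its own to reproduce. The dates come from the document; survival and accrual are assumptions.

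**1. Calendar.** January 2018 to April 2022 is 52 months before recruitment opened. January 2018 to April 2021 is 40 of them, and 40/52 = 77%. Any patient diagnosed in those 40 months and first consented in May 2022 or later has already survived at least a year. For diagnoses from May 2021 to April 2022 the first year is only partly immortal.

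**2. Mechanism.** Let λ be the true hazard and f(t) the share of patients counted at risk at time t after diagnosis who have by then registered. Deaths can be observed only among the registered, so the uncorrected hazard is λ·f(t). It is below λ whenever f(t) < 1, so the direction does not depend on the survival assumed.

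**3. Size.** Assumptions: uniform diagnosis dates from January 2018 to the cut date; constant hazard; registration at the later of diagnosis and 1 May 2022, if alive; all survivors registered. With 5-year survival of 60%, λ = −ln(0.60)/5 = 0.1022 per year, so 1-year survival is exp(−0.1022) = 90.3%. Simulation with 400,000 patients per scenario (repeat runs differ by about 0.1 point):

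| Cohort and cut | Uncorrected 1-year (true 90.3%) | Uncorrected 5-year (true 60%) |
|---|---|---|
| Diagnosed from 2018, end-2030 | 92.8% (+2.5) | 64.7% (+4.7) |
| Diagnosed from 2018, start-2026 | 94.6% (+4.3) | 68.8% (+8.8) |
| Diagnosed from 2021 only, end-2030 | 91.0% (+0.7) | 60.6% (+0.6) |

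Rough check with step 2: at the end-2030 cut 29% of enrolled patients are prevalent at entry, so f is about 0.71 early on, and exp(−0.1022 × 0.71) = 93.0%, close to 92.8%. First-year mortality falls from 9.7% to 7.2%, so (9.7 − 7.2)/9.7 = 26% of it is hidden. At start-2026 the figure is (9.7 − 5.4)/9.7 = 44%.

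**4. Range.** With assumed true 1-year survival of 70%, 80% or 90% (diagnoses 2018 to 2029, analysed at end-2030), the uncorrected estimates are 75.2%, 84.3% and 92.7%. In this simple setting a delayed-entry Kaplan-Meier returns 69.9%, 79.9% and 90.0%. If only 2018 to 2020 diagnoses are used, nobody is at risk in year 1, and even the delayed-entry estimate is 100% by construction.

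**5. Entry at recurrence.** Assumed yearly hazards: recurrence 0.12, death without recurrence 0.03, death after recurrence 0.5. Suppose 20% of patients reach the centre only at recurrence, with an end-2030 cut. True 5-year survival is 60.5%, the uncorrected estimate 62.7%, and delayed entry for everyone 56.5%. Patients registered within three months of diagnosis give 60.5% (within about half a point of the truth in repeat runs). With 10% to 50% late referrals, delayed entry for everyone gives 58.7% down to 47.3%. Applied to the whole cohort, delayed entry can therefore lie further from the truth than doing nothing.

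**The case against.** The strongest reply is that this is a condensed article with a general analysis plan. Each research question gets its own study protocol and ad hoc analysis plan, directed acyclic graphs are foreseen to identify sources of bias, and risk-set entry is the kind of detail such plans settle. It is true that the article does not commit to an uncorrected analysis. A reader might infer that it specifies a Cox model with everyone at risk from diagnosis; it only names Cox models. What remains is that the inclusion rule and the 1-year outcomes are fixed here and together create the selection, while the general plan and the limitations do not recognise it. Marginal structural models address time-varying confounding and leave delayed entry untouched.

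Three further points stand in part:

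- **Time origin.** None is stated. Counting from enrolment would remove the immortal time, but would describe survival from registry entry in a mixed-phase cohort, which is hard to set against population data. Collecting the entire course points to diagnosis without proving it.
- **Consent date.** That patients from 2021 onwards must be alive in May 2022 is inferred from two sections read together. Existing national, regional or hospital databases are listed as sources and might hold earlier consent or deceased cases. The article states no such exception, but does not rule it out.
- **Population comparison.** It is planned as a test of representativeness. A reader might infer that it is meant to show an expert-centre advantage; the article does not say so. The comparison might expose the selection but would not correct it.

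**Conclusion.** The point holds in conditional form. If survival is counted from diagnosis and consent is first obtained from May 2022, prevalent entrants carry immortal time, overall survival is biased upward by this route, and 1-year survival is guaranteed for those diagnosed before about May 2021. Under the stated assumptions the excess at the planned completion is about 2.5 points at 1 year and 4.7 points at 5 years. It is larger at earlier analyses and under 1 point for the 2021-onward group alone. The sizes are illustrative: survival, accrual and complete enrolment are assumed, and each centre may choose how many patients it enters. Late-phase entry pulls the other way, so the net error in a mixed cohort depends on the referral pattern.

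Two stronger readings are tempting. One is that most first-year mortality disappears: an end-2023 cut would give 96.6% against 90.3%, hiding about 65% of it, but the article plans no analysis at that date. The other is that delayed entry restores the true survival. It does so only if entry is unrelated to disease course, and the inclusion criteria admit patients at recurrence and metastatic phase.

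**What to change.** In the Data analyses plan:

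1. State the time origin of each time-to-event outcome. Record the dates of diagnosis, first contact with the centre, and consent or registration, and confirm in the code book that these variables exist; the article does not show it.
2. Base the 1-year outcomes, and overall and disease-free survival from diagnosis, primarily on patients registered at or near diagnosis or first treatment.
3. Add prevalent patients who reached the centre before recurrence with delayed entry at consent or registration, using left-truncated Kaplan-Meier and Cox analyses. They contribute only time after entry, which includes part of the first year for those registered within a year of diagnosis.
4. Analyse patients who reached the centre at recurrence or metastatic phase from the start of that phase, with delayed entry at registration. Do not pool them into survival from diagnosis.

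In the Discussion, name prevalent-case survivor selection as a limitation and restrict the comparison of prognosis with population-based data to the incident cohort.

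The cost is analysis wording and the confirmation, or addition, of a few dates. The downside is smaller early risk sets and wider intervals, which will be felt most at the rarest sites.

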### Sample size

This is an observational clinical registry which implies a long-term data collection lasting until all the registry objectives are met. Only HCPs that treat at least 100 cases a year of all rare head and neck cancers are EURACAN member. As of April 2022, the registry is activating 10 HCPs and, with time, is envisioning to at least duplicate the number of data providers. Considering that we expected 6 centres in Italy, 2 centres in Germany, 1 centre in Czech Republic, 1 centre in Spain, 2 centres in France (400 cases per year)and the whole rare head and neck cases in The Netherlands (300 patients yearly, based on incidence estimations), we expect about 1700 patients with a rare head and neck cancer yearly.

Due to the observational nature of the registry, sample size justification is based on the precision of the estimates presented in terms of width of two-sided 95% Confidence Interval (CI) for a single proportion using the Simple Asymptotic method (in case of categorical variables) and in form of normal distribution for means (in case of continuous variables). Thus, for example, for a categorical endpoint (e.g., proportion) a sample size of 80 patients (e.g. middle ear cases in 4 years) will achieve a maximum width of 95% CI on estimated proportions of 23.4% (i.e. estimated proportion +/- 11.7%). For continuous endpoints, a sample size of 80 patients will achieve a maximum width of 95% CI on estimated means of 0.46*SD (i.e. estimated mean +/- 0.23*SD, where SD = Standard Deviation).

Table 1 reports the precision of the estimates for categorical and continuous endpoint under different sample size.

**Table 1 pone.0283071.t001:** Precision of the estimates expressed as 95% Confidence Interval (CI) for categorical and continuous endpoint accordingly to different sample size.

		
	Categorical endpoint		Continuous endpoint	
Target sample size	max 95% CI	Width of 95% CI (%)	max 95% CI	Width of 95% CI
1000	Estimate +/-0.03	0.06	Estimate +/- 0.06*SD	0.12*SD
250	Estimate +/- 0.06	0.12	Estimate +/- 0.12*SD	0.24*SD
80	Estimate +/- 0.11	0.22	Estimate +/- 0.22*SD	0.44*SD
70	Estimate +/- 0.12	0.24	Estimate +/- 0.23*SD	0.46*SD
60	Estimate +/- 0.13	0.26	Estimate +/- 0.25*SD	0.50*SD
50	Estimate +/- 0.14	0.28	Estimate +/- 0.27*SD	0.55*SD

For the analytical questions involving several different outputs and variables, it is not possible to define a summary of the sample size calculation. For this reason ad hoc analysis plans for each research question are envisioned.

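### The worked precision example for 80 patients quotes confidence interval widths that belong to 70 patients, and disagrees with Table 1; the error is small and conservative

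*Protocol article*

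**What the plan says.** The Sample size section of the protocol article rests its justification on the precision of estimates. For categorical variables the measure is the "width of two-sided 95% Confidence Interval (CI) for a single proportion using the Simple Asymptotic method". For continuous variables the interval is "in form of normal distribution for means (in case of continuous variables").

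The section then gives one worked example, "a sample size of 80 patients (e.g. middle ear cases in 4 years"). For a proportion, this sample size "will achieve a maximum width of 95% CI on estimated proportions of 23.4% (i.e. estimated proportion +/- 11.7" per cent). For a mean, "a sample size of 80 patients will achieve a maximum width of 95% CI on estimated means of 0.46*SD", that is, a half-width of 0.23*SD.

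Table 1 follows immediately and lists precision for six sample sizes. The two rows that matter here are:

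- n = 80: proportion +/- 0.11, width 0.22; mean "Estimate +/- 0.22*SD", width 0.44*SD.
- n = 70: proportion +/- 0.12, width 0.24; mean +/- 0.23*SD, width 0.46*SD.

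**The concern.** For the same sample size, the text and the table give different precision for both kinds of endpoint. Rounding does not explain it: a half-width of 11.7% would appear in the table as 0.12, not 0.11, and 0.23*SD is not a rounding of 0.22*SD. One of the two must be wrong.

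The example matters to the extent that precision is the stated basis for the sample size. It is the only case put into words, and it concerns the rarest tumour group in the registry. The section Data analyses, and the remark that closes Sample size, leave analytical questions to separate plans, so a reader looking for the promised precision in middle ear cancer will look here and find two answers.

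**Working it through.** **Inputs**, all from the Sample size section: n = 80; two-sided 95% interval, so z = 1.96; simple asymptotic (Wald) interval for a proportion, where a maximum width means p = 0.5; normal interval for a mean.

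**Formulas**

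- Proportion: half-width = 1.96 × √(0.25/n).
- Mean: half-width = 1.96 × SD/√n.
- Width = 2 × half-width.

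**Table 1, row for 80, is reproduced**

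- Proportion: 1.96 × √(0.25/80) = 0.1096; width 0.2191. Printed: 0.11 and 0.22.
- Mean: 1.96/√80 = 0.2191*SD; width 0.4383*SD. Printed: 0.22*SD and 0.44*SD.

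**The text's figures for 80 are not reproduced, but they are at n = 70**

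- Proportion: 1.96 × √(0.25/70) = 0.1171; width 0.2343. To one decimal this is +/- 11.7% and 23.4%, exactly as in the text.
- Mean: 1.96/√70 = 0.2343*SD, which rounds to 0.23*SD. The unrounded width is 0.4685*SD; doubling the rounded half-width gives 0.46*SD, as in the text and in Table 1's row for 70.

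**Inverting the formulas**

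- A half-width of 11.7% needs n = (1.96 × 0.5/0.117)² = 70.2, or 69.6 to 70.8 if the true value lies anywhere between 11.65% and 11.75%.
- A half-width of 0.23*SD needs n = (1.96/0.23)² = 72.6, or 69.6 to 75.9 for values between 0.225 and 0.235.

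Both ranges contain 70 and neither contains 80.

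**Would another method rescue the text at n = 80?**

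| Method at n = 80 | Width |
|---|---|
| Wald with continuity correction | 23.2% (+/- 11.6%) |
| Clopper-Pearson | 22.8% |
| Wilson | 21.4% |
| Mean, t quantile | 0.445*SD (+/- 0.223*SD) |

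None gives 23.4% or 0.46*SD, and none is the method named.

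**Size of the error**: 23.4 − 21.9 = 1.5 percentage points, and 0.46 − 0.44 = 0.02*SD.

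**Other cells of Table 1.** At n = 50 the half-width for a mean is 1.96/√50 = 0.277*SD, so 0.28; the table prints 0.27, although its width of 0.55 is right. The width column for proportions is headed with a per cent sign but holds fractions. Several other widths are doubled rounded half-widths. Rounding from the unrounded half-width would instead give:

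| Cell | Unrounded width | Would print | Prints |
|---|---|---|---|
| n = 60, proportion | 0.253 | 0.25 | 0.26 |
| n = 60, mean | 0.506*SD | 0.51 | 0.50 |
| n = 70, proportion | 0.234 | 0.23 | 0.24 |
| n = 70, mean | 0.469*SD | 0.47 | 0.46 |
| n = 250, mean | 0.248*SD | 0.25 | 0.24 |

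These follow a rounding convention and are not wrong calculations.

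**The case against.** The best defence is that this is a slip in an illustration. The sentence is offered as an example, Table 1 has the values for 80 correct to two decimals, and the registry collects data until its objectives are met, so no target number, stopping rule or test rests on the figure. The error also runs in the safe direction: the text states a wider interval than 80 patients give. All of this stands, and it limits the weight of the point. It does not remove the contradiction.

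A reader might go further and infer that the plan leaves open whether 70 or 80 middle ear cases are expected. The documents give little support for that. The text prints 80 twice, Table 1 has a row for 80, and nowhere are 70 middle ear cases mentioned. The figures fit 70, but that does not show that 70 was the planned count.

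A reader might equally try to prove from accrual that 80 is right. With 1,700 patients a year for 4 years and the incidence rates in the Introduction, 1700 × 4 × 0.03/(0.5 + 0.5 + 1.5 + 0.03) = 80.6. But the annual case counts given in the same paragraph yield 1700 × 4 × 200/(2,500 + 2,500 + 8,000 + 200) = about 103. Both results assume that the registry's case mix follows incidence. The inclusion criteria also admit tumours at other sites and let each provider limit how many patients it enters. The range of 81 to 103 is therefore an assumption and cannot settle which figure slipped.

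**Conclusion.** The point holds as an arithmetic inconsistency. By the stated methods at p = 0.5, the text overstates the width at n = 80 by about 1.5 percentage points for a proportion and about 0.02*SD for a mean, and it contradicts Table 1. The figures it prints belong to n = 70. The documents do not show whether the sample size or the widths were left uncorrected.

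The consequence is small and conservative, and enrolment, analysis and conduct are unaffected. It would be wrong to conclude that the precision justification as a whole fails, or that Table 1 is generally in error: its row for 80 is right, and apart from the half-width for a mean at n = 50 and the column heading, its departures come from doubling rounded half-widths.

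**What to change.** Make the text agree with Table 1 in one of two ways:

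- keep n = 80 and state a maximum 95% interval width of 21.9% (+/- 11.0%) for a proportion and 0.44*SD (+/- 0.22*SD) for a mean; or
- if 70 middle ear cases is the intended count, change 80 to 70 in both places where it appears in the example.

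Optionally, in Table 1, correct the half-width for a mean at n = 50 to 0.28*SD and remove the per cent sign from the heading of the width column. Leave the other cells alone unless every width is recomputed from unrounded half-widths; in that case both widths at n = 60 and at n = 70, and the width for a mean at n = 250, change together.

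The cost is a correction to the worked example and at most a few table entries, with no effect on conduct.
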